## Abstract

**Background:**

Chronic pain is a major source of human suffering, and chronic low back pain (cLBP) is among the most prevalent, costly, and disabling of pain conditions. Due to the significant personal and societal burden and the complex and recurring nature of cLBP, self-management approaches that can be practiced at home are highly relevant to develop and test. The respiratory system is one of the most integrated systems of the body, and breathing is bidirectionally related with stress, emotion, and pain. Thus, the widespread physiological and psychological impact of breathing practices and breathwork interventions hold substantial promise as possible self-management strategies for chronic pain. The primary aim of the current randomized pilot study is to test the feasibility and acceptability of a conscious connected breathing with breath retention intervention compared to a sham control condition.

**Methods:**

The rationale and procedures for testing a 5-day conscious connected breathing with breath retention intervention, compared to a deep breathing sham control intervention, in 24 adults (18–65 years) with cLBP is described. Both interventions will be delivered using standardized audio recordings and practiced over 5 days (two times in-person and three times at-home), and both are described as Breathing and Attention Training to reduce possible expectancy and placebo effects common in pain research. The primary outcomes for this study are feasibility and acceptability. Feasibility will be evaluated by determining rates of participant recruitment, adherence, retention, and study assessment completion, and acceptability will be evaluated by assessing participants’ satisfaction and helpfulness of the intervention. We will also measure other clinical pain, psychological, behavioral, and physiological variables that are planned to be included in a follow-up randomized controlled trial.

**Discussion:**

This will be the first study to examine the effects of a conscious connected breathing with breath retention intervention for individuals with chronic pain. The successful completion of this smaller-scale pilot study will provide data regarding the feasibility and acceptability to conduct a subsequent trial testing the efficacy of this breathing self-management practice for adults with cLBP.

**Trial registration:**

Clinicaltrials.gov, identifier NCT04740710. Registered on 5 February 2021.

**Supplementary Information:**

The online version contains supplementary material available at 10.1186/s40814-023-01247-9.

## Background

Chronic pain is a major public health problem. Chronic low back pain (cLBP), one of the most prevalent chronic pain conditions, affects more than 540 million people and is a leading cause of disability in the world [1, 2]. The significant direct (e.g., healthcare) and indirect costs (e.g., work disability, loss of productivity) associated with cLBP produce substantial personal and societal burden, which is expected to increase over the coming years [1, 3]. Although cLBP tends to resolve over time, there are high rates of recurrence and many people suffer indefinitely [4]. Nonpharmacological interventions, including complementary and integrative approaches, continue to gain interest and are now recommended as first line treatments for cLBP [5, 6]. Due to the persistent, costly, and complex nature of cLBP, nonpharmacological self-management approaches rooted in the biopsychosocial model of chronic pain are of great interest to develop and test [3, 5, 7–16].

Self-management approaches include strategies or interventions that individuals can learn and apply on their own to prevent or relieve symptoms, such as pain or stress [17, 18]. These approaches empower individuals with tools, knowledge, or techniques to take an active role in their health and symptom self-management. This is in contrast to traditional healthcare models where a patient is a passive recipient of care (e.g., surgery). Some examples of self-management approaches for chronic pain include physical exercise, mindfulness meditation, diet, and the use of medical or non-medical devices (e.g., transcutaneous electrical nerve stimulation) [5, 19]. Research shows that people with chronic pain value self-management approaches that (1) they can engage in at-home or remotely, (2) they can apply while continuing their medication, (3) improve more than just pain symptoms (e.g., depression), and (4) have a low time burden [20, 21]. We propose that brief, daily breathing practices are promising self-management approaches to investigate as they align with stakeholder values and potentially offer a nonpharmacological, biopsychosocial, and scalable solution to reduce the global burden of cLBP.

There are a variety of breathwork interventions (i.e., conscious breathing practices) that may be helpful for managing and treating chronic pain [22–26]. For example, increasing evidence supports that slow deep breathing and paced breathing (e.g., respiratory biofeedback) can improve pain-related outcomes and mechanisms, including increased parasympathetic nervous system activity (i.e., heart rate variability), baroflex sensitivity, and relaxation, and decreased stress, anxiety, depression, negative affect, muscle tension, and experimental pain sensitivity [27–38]. These studies, however, primarily examine the effects of controlled breathing practices in healthy samples. Research on breathing practices for those with chronic back pain shows small-to-large effects for improving pain [23–25], but more randomized trials with rigorous methods are needed. Moreover, substantially less research has investigated other types of breathing interventions that may be more potent than slow deep breathing or other similar relaxation-based self-management practices (e.g., meditation) [39]. Specifically, c*onscious connected breathing*, a technique at the core of many different breathwork interventions [40–45], involves breathing with no pause between inhalation and exhalation (also known as circular breathing). Breathwork interventions that use conscious connected breathing often include other “add-on” components, such as mindful body awareness, music, or movement, that are believed to increase their efficacy [46]. The breathing practice investigated in the current study combines conscious connected breathing with periods of breath holding, or breath retention.

The empirical research on conscious connected breathing with breath retention (CCBR) comes from an intervention that is often delivered by a specific teacher (i.e., Wim Hof^1^) within a group retreat setting and combined with additional components (e.g., cold exposure, visualization meditation, strength exercises) [47–50]. These aspects limit accessibility to the intervention and also complicate conclusions that can be drawn regarding the efficacy and mechanisms of the intervention due to the many potential specific and non-specific treatment effects [51–56]. Nevertheless, studies suggest that the breathing and retention practice alone can reduce stress [57] and induce profound physiological changes, including safe respiratory alkalosis (i.e., rise in pH levels), intermittent hypoxia, immediate changes in metabolic and hormonal activity (e.g., increased gluconeogenesis, human growth hormone), and increases in plasma epinephrine levels associated with sympathetic nervous system activation [47–49, 56, 58–60]. CCBR also seems to have significant effects on the immune system, demonstrated by an increase in anti-inflammatory and decrease in pro-inflammatory cytokines following the administration of an endotoxin [48, 56]. Furthermore, the full intervention that included cold exposure and strength exercises was shown safe and feasible for patients with axial spondyloarthritis, a chronic inflammatory disease characterized by pain, with preliminary evidence for reductions in systemic inflammation and disease severity [47]. Yet, CCBR alone has not been tested for its impact on chronic pain, including in those with cLBP.

Consistent with models and recommendations for developing theoretically informed interventions [61, 62], several lines of evidence support the premise that CCBR will be helpful for individuals with chronic pain. First, both the volitional control of breathing and the specific type of rhythmic connected breathing and breath holding technique used in CCBR can elicit a cascade of biological and physiological responses that may reduce pain, such as improvements in heart rate variability (HRV) [26, 63, 64], baroreceptor sensitivity [65–68], acid-base balance (respiratory alkalosis) [69–71], periaqueductal gray structure and function [72–76], and immune and metabolic activity (e.g., inflammation) [47–49, 58, 77, 78]. Second, both the cyclical breathing and the breath retention may serve as a mild stressor (i.e., hormesis), like physical exercise, where the acute challenge to breathe deeper and hold one’s breath for longer than usual results in adaptive changes (e.g., stress resilience, preparation for oxidative stress, carbon dioxide tolerance) [41, 59, 79–84]. Third, conscious breathing exercises are likely to increase mindfulness and interoception (i.e., attention to and awareness of body, feelings, and homeostatic signals) [35, 85, 86]—both considered key factors for self-managing chronic pain as well as for improving overall mental and physical health [87–89]. Last, the extended breath retention (1–2.5 min) may induce intermittent hypoxia, which has been shown to lead to improved respiratory and non-respiratory motor function and neuroplasticity [90–92]. Enhanced neuroplasticity may open a therapeutic window that when combined with existing pain treatments, such as relaxation or mindful body awareness, can have synergistic effects in improving pain-related outcomes [92–97]. While this list is far from exhaustive, these possible mechanistic pathways provide compelling justification to scientifically investigate the physical and psychological effects of CCBR in those with chronic pain.

The purpose of the current pilot study is to evaluate whether it is feasible to conduct a clinical trial investigating CCBR for adults with cLBP in preparation for a subsequent, adequately powered randomized controlled trial (RCT) [98–101]. The primary objective is to test the feasibility and acceptability of 5 days of CCBR practice delivered via standardized audio recordings, compared to a structurally equivalent deep breathing sham control intervention [102–104], in a sample of 24 adults with cLBP. We expect it to be feasible to recruit, retain, and randomize participants to the intervention groups and expect at least 70% of participants to rate the interventions as acceptable and satisfying (≥ 7 out of 10). The secondary objective is to gather data regarding the plausibility that the CCBR intervention can result in clinically meaningful improvements in pain and pain-related variables [100, 105]. To demonstrate plausibility of improvement, we expect a greater ratio of participants in the CCBR group, compared to the control group, will meet the clinically significant treatment response target of ≥ 30% improvement in pre-post average pain intensity ratings [106–108]. A 30% reduction in pain is considered a moderately important change following treatment and is commonly used to determine clinical significance and/or treatment response in pain RCTs [107–111]. Results from this study will not be used to make claims about preliminary efficacy or to determine power for future sample size calculations [98, 100, 112] but rather to provide feasibility estimates, refine the interventions, and inform the successful design and implementation of an anticipated RCT, which will rigorously test the efficacy and mechanisms of this self-management breathing practice for adults with cLBP.

## Methods

### Study design

This parallel group, pilot RCT is designed to examine the feasibility and acceptability of a 5-day conscious connected breathing intervention that includes brief periods of breath retention, compared to a deep breathing sham control intervention, in a sample of adults with cLBP. The intervention length (5 sessions, 17-min per session) was chosen because previous research has demonstrated that mind-body interventions can influence physiological mechanisms of interest, such as central and autonomic nervous system functioning, after a similar period of training [113]. Both interventions will be described as Breathing and Attention Training and neither will be depicted as the active therapeutic intervention (i.e., single-blind) in order to reduce possible expectancy and placebo effects common in pain research [102, 104, 114]. Participants will be randomly assigned at a 1:1 ratio to either the Standard-Breathing and Attention Training or the Focused-Breathing and Attention Training (BAT). The Standard-BAT is the sham control intervention, and the Focused-BAT is the active CCBR intervention. All participants will provide written and signed informed consent. The study was approved by the University of Florida Institutional Review Board, registered on clinicaltrials.gov (NCT04740710), and designed in accordance with CONSORT guidelines for reporting pilot RCTs [101, 115–117]. See Fig. 1 below for an overview of the study design.

**Fig. 1 Fig1:**
[figure not shown]
Overview of study design

### Procedure

Interested participants will complete a telephone screening to determine initial eligibility, and those who qualify will be scheduled for their first visit at the University of Florida Pain Clinical Research Unit to obtain informed consent and complete several baseline assessments and physical functioning tasks. At the end of Visit 1, participants will be scheduled for two additional study visits to occur within a 1-week period (pre-intervention and post-intervention). Participants will also be asked to complete two additional baseline surveys online using REDCap between Visit 1 and Visit 2, which is intended to reduce the participant burden and length of Visit 1. At Visit 2 (pre-intervention), participants will be randomized to the Standard- or Focused-BAT intervention before undergoing quantitative sensory testing procedures. Then, participants will be instructed via an audio-recording to practice their assigned breathing intervention for the first time with the researcher. Physiological data will be collected before, during, and after the breathing practice at both Visit 2 and Visit 3. Following Visit 2, participants will receive an email to practice BAT first thing in the morning if possible by following along to the recording on their own at home. If not possible to practice upon awakening, participants will be asked to practice at least 2 h after a meal. We will attempt to schedule intervention sessions over five consecutive days when possible (Monday–Friday). When not possible, we will require that the last at-home session and last in-person session (BAT sessions 4 and 5) be practiced on consecutive days. At Visit 3, participants will practice their assigned breathing intervention for the 5th and final time and then complete post-intervention questionnaires, quantitative sensory testing procedures, and physical functioning tasks. Finally, participants will be asked to complete 1-, 2-, and 3-month follow-up surveys online using REDCap.

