### Randomization and blinding

The principal investigator ([name]) generated the allocation sequence with a block size of two using an online random number generator (Random.org). Based on the allocation sequence, participants will be randomized (1:1 ratio) using the REDCap Randomization Module at the beginning of Visit 2 to either the Focused- or Standard-BAT. Participants will not be told which intervention they were randomized to until the end of the study, after the 3-month follow-up survey. Due to the inherent difficulties of blinding behavioral interventions, only the participant—not the researcher—will be blind to intervention assignment [102, 114, 120]. Effectiveness of participant blinding will be reported.

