Michigan Body Map [141, 142]		X					
Patients’ Global Impression of Change [143–145]				X	X	X	X
Oswestry Disability Index [146]		X		X	X		X
Pain Catastrophizing Scale [147]		X		X	X		X
Pain Self-Efficacy Questionnaire [148]		X		X	X		X
Perceived Stress Scale [149]		X		X	X	X	X
Generalized Anxiety Disorder 2-item [150]		X		X	X	X	X
Multidimensional Assessment of Interoceptive Awareness-2 [151]		X		X	X		X
Multidimensional Psychological Flexibility Inventory^a^ [152, 153]		X		X	X		X
Physical and physiological assessments							
Back performance scale [154]		X		X			
Short performance physical battery [155]		X		X			
Quantitative sensory testing [156, 157]			X	X			
Heart rate variability			X	X			
Oxygen saturation			X	X			
Blood pressure		X	X	X			

^a^Assessment will be completed online between Visit 1 and Visit 2

*NIH* National Institutes of Health, *PROMIS* Patient-Reported Outcomes Measurement Information System

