#### Quantitative Sensory Testing (QST)

We will use QST to determine pain modulatory balance via pressure pain threshold (PPT), temporal summation (TS) of mechanical pain, and conditioned pain modulation (CPM). First, to determine PPT, a handheld pressure algometer with a 1-cm^2^ tip (Medoc, Ltd., AlgoMed, Ramat Yishai, Israel) will be applied to the participants trapezius muscle at a steadily increasing rate of pressure. The participant will press a button when the pressure sensation first becomes painful. This procedure will be repeated five times on the same trapezius muscle, and the mean pressure rating across the five trials will be used for analyses on remote pain sensitivity. Second, to determine remote and local TS of mechanical pain, we will use a 300 *g* nylon monofilament (Touchtest Sensory Evaluator 6.65) to deliver a pinprick sensation to the back of the hand (remote) and lumbar spine (local). A single pinprick stimulus will be delivered and the participant will give a verbal pain rating from 0 (no pain) to 100 (most intense pain imaginable). Then, a series of 10 stimuli (once per second) will be delivered to the same location, and the participant will again give a rating of the greatest pain intensity experienced during the 10 stimuli. This procedure will be repeated twice at each site (back of each hand and bilaterally on lumbar spine) and the trials for each site will be averaged. TS will be used as an indicator of pain facilitation and calculated for each site by subtracting the average rating of the single stimulus from the 10 repeated stimuli. Third, to determine CPM, the test stimulus will be PPT at the trapezius, as described above, and the conditioning stimulus will be immersion of the hand (contralateral to the PPT) in cold water for 1 min at 12 °C (ARCTIC A25 refrigerated bath with an SC150 immersion circulator; ThermoFisher Scientific, USA). PPT will be assessed immediately before cold water immersion, 30 s after immersion, and immediately after withdrawing the hand from immersion. CPM will be used as an indicator of pain inhibition and will be calculated by subtracting the PPT before immersion from the PPT during immersion.

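### Randomising before the only pre-intervention sensory testing, with a researcher who is not blind, opens an avoidable route for bias into the QST baseline, chiefly the pressure pain threshold

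*Protocol article*

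**What the plan says.** The protocol article gives the order of events twice. Under Procedure: "At Visit 2 (pre-intervention), participants will be randomized to the Standard- or Focused-BAT intervention before undergoing quantitative sensory testing procedures". Under Randomization and blinding, allocation is made "using the REDCap Randomization Module at the beginning of Visit 2 to either the Focused- or Standard-BAT". The same section states that "only the participant—not the researcher—will be blind to intervention assignment", and that the principal investigator "generated the allocation sequence with a block size of two using an online random number generator".

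Table 2 (Baseline assessment and secondary outcomes) marks QST, heart rate variability and oxygen saturation at Visits 2 and 3 only. Blood pressure is marked at Visits 1, 2 and 3. The PROMIS scales, the other outcome questionnaires and the physical functioning tests have their baseline at Visit 1. On physiology, Procedure says: "Physiological data will be collected before, during, and after the breathing practice at both Visit 2 and Visit 3".

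In the QST section the handheld algometer "will be applied to the participants trapezius muscle at a steadily increasing rate of pressure", and the participant presses a button when the pressure first becomes painful. Temporal summation (TS) and conditioned pain modulation (CPM) are each a difference between two readings within a session. Statistical analyses plans univariate tests of group equivalence on baseline and outcome variables, and names QST among the covariates and predictors of response to be explored.

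**The concern.** A baseline is best fixed before anyone who measures it can know the arm. Here the only pre-intervention QST comes after allocation, by staff who are not described as blind. The article attributes the lack of researcher blinding to the difficulty of blinding behavioural interventions. That explains unblinded staff once the breathing session starts, but gives no reason to open the allocation before tests that do not depend on the arm.

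The team also has a directional expectation: the Discussion expects the control to be less effective than the active arm. If that expectation moves baseline readings in one arm, the shift enters any pre-post comparison with the opposite sign and contaminates QST as a covariate or predictor. The Discussion describes the pilot as a smaller version of the efficacy trial with the same procedures, so the order would be carried into a study meant to test efficacy and mechanisms.

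**Working it through.** **Order of events.** Procedure and Randomization and blinding agree: allocation at the start of Visit 2, then QST, then the first breathing session. Table 2 offers no earlier QST value. The post-allocation QST baseline is therefore stated outright, not inferred from silence.

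**Exposure, measure by measure.**
- Pressure pain threshold: the examiner applies a handheld device and controls the pressure ramp. This is the most exposed measure, although a blind participant presses the button and five trials are averaged.
- TS (ten stimuli minus one stimulus) and CPM (threshold during immersion minus threshold before it): an additive operator shift that is constant within the session cancels. Only different handling of the two readings would bias them.
- Resting heart rate variability and oxygen saturation: instrument recordings of a blind participant lying still, so only slightly exposed.
- Blood pressure: a Visit 1 value also exists, before randomisation.
- Feasibility, acceptability and the 30% pain response: not affected.

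**The plan's own figure.** 24/(1 − 0.20) = 30 recruited, as stated. The 24 completers at 1:1 give 12 per arm.

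**Illustrative size.** The document gives no SD, no correlation and no estimate of tester effects, so every value here is assumed. Let one arm's QST mean be shifted by b2 SD at Visit 2 and b3 SD at Visit 3, with equal SDs and pre-post correlation ρ.
- Bias in the change-score difference = b3 − b2. With b3 = 0 and b2 = b, it is −b.
- Bias after baseline adjustment = −ρb.
- SE of the change-score difference, 12 per arm = √(4(1 − ρ)/12) SD.

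| ρ | SE (SD) | b = 0.2: b/SE | b = 0.5: b/SE | Size of adjusted bias, b = 0.2 / 0.5 |
|---|---|---|---|---|
| 0 | √(4/12) = 0.58 | 0.35 | 0.87 | 0 / 0 |
| 0.5 | √(2/12) = 0.41 | 0.49 | 1.22 | 0.10 / 0.25 |
| 0.8 | √(0.8/12) = 0.26 | 0.77 | 1.94 | 0.16 / 0.40 |

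**Would the planned baseline test reveal it?** The SE of a baseline difference is √(2/12) = 0.41 SD. By the normal approximation at two-sided 5%, a shift of 0.2 SD is detected with probability about P(Z > 1.96 − 0.49) = 7%, and 0.5 SD with about P(Z > 1.96 − 1.22) = 23%. The equivalence test offers little protection.

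**Effect of block size.** With fixed blocks of two, staff who know the first assignment of a pair can deduce the second. In 30 participants that is 30/2 = 15. Reordering alone therefore protects only about half.

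**The case against.** The strongest reply is that little in this pilot depends on QST. The Background says results will not support preliminary efficacy claims or power calculations, the Discussion calls the improvement analyses exploratory, and no between-arm QST change-score analysis is specified. This stands, and it limits the weight of the point. It does not remove it: QST is still compared between groups and explored as a covariate or predictor.

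A reader might infer that all Visit 2 baselines are compromised. The document does not support that, for the reasons given measure by measure above. Nor does it say who performs QST or when that person sees the allocation. It says the researcher is not blind and names no blind tester, and a condensed article may leave staffing to the full protocol.

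The sharpest technical objection concerns Visit 3. QST there has no stated blind tester either. If a tester shifted one arm equally at both visits (b3 = b2), the change score would be unbiased under the present order, and removing only the Visit 2 shift would leave b3 uncancelled. This is correct. It is no reason to keep an exposed baseline, because equal shifts at the two visits cannot be assumed and a covariate or predictor uses the baseline alone. It does mean that reordering is not a complete cure.

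**Conclusion.** The point holds for the Visit 2 QST baseline, mainly the pressure pain threshold. The order of events and the unblinded researcher are both stated, and the order is avoidable. It is a moderate design weakness: worth correcting, but no threat to the pilot's primary outcomes or its pain-response measure.

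Its size is unknown. The 0.2 to 0.5 SD bias assumes a shift of that size in one arm at Visit 2 only. Its ratio to the standard error runs from 0.35 to 1.94, depending on the shift and on a pre-post correlation between 0 and 0.8. A reader might prefer one headline ratio, but any such figure hides a choice of both values. A reader might also infer that bias has been shown; the document shows only a way in which it could arise.

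**What to change.** At Visit 2, complete QST, blood pressure and the 5-minute resting recording first. Then open the REDCap allocation, introduce the breathing training and start the first session. Amend Procedure and Randomization and blinding to match. No outcome questionnaire needs to move: apart from QST and the physiological measures, Table 2 lists only treatment expectations and adverse events at that visit.

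Replace the fixed block of two with larger or varied blocks, so that the second assignment of a pair cannot be deduced before testing. State as a limitation that Visit 3 QST has no stated blind tester, which reordering does not cure.

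The cost is small: a revised visit checklist and a new allocation list. Recruitment stays at 30 for 24 completers, with no added test or visit. The order change without the block change gives only partial protection.
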